#### Primary outcomes

3.8.1

Risk of fall: Falls risk will be evaluated using the Downton Fall Risk Index (DFRI), a five-item composite score based on prior falls, medication, sensory deficits, mental state, and mobility. A score of less than three points means low risk of fall, and a total score above three points indicates a high risk of fall (Downton index, 2016).

Balance: Dynamic balance will be measured with the Timed Up and Go (TUG) test, which evaluates the time in seconds that a participant takes to rise from a chair, walk 3 m, turn, return, and sit down again (Mancilla et al., 2015) The test will be assessed three times, and the best attempt will be recorded. While static balance will be measured thought the single-Leg Stance Test, where participants must maintain balance on one leg for at least 5 s (Mancilla et al., 2015) The test will be assessed three times, and the best attempt will be recorded.

Posturography: Romberg quotient and C90 area will be measured (Smart Balance Hur® Labs model BTG4-F, Kokkola, Finland). Posturography records center of pressure displacement while standing on a stable platform (Furman, 1994; Visser et al., 2008). Participants must maintain a bipedal posture with feet shoulder width apart, hands hanging at the sides of the body and head facing forward. They must also follow the evaluator’s instruction, either eyes open (condition 1) or closed (condition 2). The foot resting points on the platform are marked to ensure repeatability.

Functional independence: this outcome will be measured with Functional Independence Measure (FIM) scale, it consists of 18 items that assess both motor and cognitive skills, and is scored on a 7-level scale, where one indicates total dependence and seven complete independence (Paolinelli et al., 2001).

Cardiorespiratory fitness: Aerobic capacity will be measured by the 2-Minute Walk Test, which measures the total distance (in meters) covered at a self-selected walking pace within 2 min on a flat surface, a full step is defined as a step performed by raising the knee to a height corresponding to the midpoint between the patella and the iliac crest (Guralnik et al., 1994).

#### Secondary outcomes

3.8.2

Body composition: Total body mass, fat mass, fat-free mass, visceral fat and segmental muscle mass of the lower limbs will be assessed using a bioelectrical impedance analyzer (InBody 270®, Biospace, Seoul, Korea) according to the manufacturer’s instructions (Sergi et al., 2015).

Upper limb strength: This will be estimated using the grip strength test, which uses a previously calibrated BASELINE® hydraulic dynamometer. The participant will sit on a chair with a backrest, with their shoulders adducted, their elbow flexed at 90°, and their forearm and wrist in a neutral position. The evaluated arm should not rest on any surface, and the dynamometer should be used in a vertical position. Participants will be asked to perform a maximum grip force with their dominant hand for 3 s, resting for 1 min between each repetition, making two attempts. The highest grip value of the repetitions will be used. This protocol has been described previously (EPI–Departamento de Epidemiologia, 2015).

Lower limbs strength: This will be measured using a five-repetition sit-to-stand test. Participants will be asked to stand up and sit down, as quickly as possible, five times from a chair without armrests located on a wall. The time will be measured from the beginning of the movement until participants manage to stand up for the fifth repetition. Arms should be crossed over the chest during the test. The time will be recorded in seconds and tenths of a second (Guralnik et al., 1994; Bohannon, 2006).

Muscle quality of the lower limb: Muscle quality will be evaluated through intramuscular fat infiltration, in which muscle echogenicity will be measured by ultrasound (Cross-sectional view of the quadriceps and tibialis anterior muscles). The images will be analyzed using ImageJ® software to calculate the gray scale intensity (0-255 arbitrary units), which reflects the intramuscular fat content and in addition the muscle architecture will be measured through muscle thickness (Lizama-Pérez et al., 2023).

Physical activity level: The level of physical activity in older adults can be measured using the IPAQ questionnaire, which has been shown to be a valid and reliable tool in older adults (Rubio Castañeda et al., 2017). Recent studies show that, although there is a tendency to overestimate physical activity, the IPAQ remains useful for population studies (Cleland et al., 2018) and has been used successfully in adults over 70 years of age, differentiating activity levels according to age and comorbidities (Ferretti et al., 2020).

Quality of life: This will use the 36-item Short Form Health Survey (SF-36) questionnaire (Vilagut et al., 2005) in its Spanish version (Alonso et al., 1995). The SF-36 is a self-report instrument that contains 36 questions from eight dimensions related to people’s health: physical function, physical role, bodily pain, vitality, social function, emotional role, mental health, and general health (Ware and Sherbourne, 1992). The score obtained corresponds to values on a scale of 0–100, where higher scores indicate better health (Ware and Sherbourne, 1992). The SF-36 is adapted and validated in Chilean older adults, presenting adequate indicators of general Cronbach’s alpha internal consistency of 0.88 (Lera et al., 2013).

Pain intensity and interference: The Brief Pain Inventory-Short Form (BPI-SF) remains one of the most validated and widely used tools for assessing pain intensity and interference across various clinical populations, especially in musculoskeletal and chronic pain conditions. Recent studies have confirmed its strong psychometric properties, including internal consistency (Cronbach’s α = 0.83–0.96), known-group validity, and responsiveness to change (U Jumbo et al., 2020). In a systematic review, the BPI-SF demonstrated a stable two-factor structure and was shown to be more robust and reliable than comparable tools such as the Short-Form McGill Pain Questionnaire-2 in musculoskeletal pain assessment (MacDermid et al., 2019). Additionally, the BPI-SF has been successfully adapted for older adult populations, including those with nociceptive, neuropathic, and nociplastic pain, with excellent test-retest reliability (ICC = 0.90–0.96) and internal consistency (α = 0.87) (Ferreira et al., 2023).

#### Sociodemographic background

3.8.3

The sociodemographic characteristics of the older adults will be recorded, including age, sex (male/female), geographic origin (rural or urban), educational level (basic education: <8 years, secondary education: 8–12 years, higher education: >12 years), and the presence of comorbidities such as diabetes mellitus, hypertension, and dyslipidemia, as well as some habits such as smoking habit and alcohol consumption. Nutritional status will be classified according to body mass index (BMI), which is obtained by dividing body weight by bipedal height squared (weight/height^2^), with cut-off points being considered, underweight <22.9 kg/m^2^, normal weight: 23.0–27.9 kg/m^2^, overweight: 28.0–31.9 kg/m^2^, and obese: ≥32.0 kg/m^2^
Reis et al., 2019. The questions and classification indicated in the National Health Survey 2016-2017 will be used (EPI–Departamento de Epidemiologia, 2015).

### Data management, data access and dissemination policy

3.9

Data collection will be carried out in a SENAMA center located in Santiago, Chile, and will be in charge of a team of four researchers, who will apply the instruments contemplated in the intervention protocol. All collected data will be anonymized at the point of entry, ensuring that no personal identifiers are stored in the database. The anonymized dataset will be stored on the institutional Dropbox® platform, which is protected by SSL/TLS encrypted transfer, AES 256-bit encryption at rest, and two-factor authentication. Access to the repository will be strictly limited to the principal investigator and co-researchers through secure institutional accounts. Data will be stored for a period of 5 years following the completion of the study, in accordance with the data protection policies of Universidad Católica Silva Henríquez and national ethical regulations in Chile (Law 20.584 on patient rights and duties). After this period, all data will be permanently deleted. The use of Dropbox® has been reviewed and approved as part of the institutional data management policy, ensuring compliance with ethical and confidentiality standards.

Once the study is completed, the results obtained will be shared with SENAMA, as well as with the academic community through presentations at specialized national and international congresses and seminars. In addition, the findings, including analyses derived from mechanical inference, will be published in scientific journals in the field, with the aim of contributing to the body of knowledge on innovative intervention strategies for older adults.

### Statistical analysis

3.10

Missing data will be handled by intention-to-treat analysis (multiple imputation method) [65]. The data will be analyzed using the intention-to-treat (ITT) strategy (Ahn and Kang, 2023). The description will be made as measures of central tendency and dispersion (continuous variables) and as percentages (categorical variables). Using the Shapiro-Wilk test, the normality of the data will be verified, and a two-step approach for transforming will be applied to the non-normal variables (A Two-Step Approach for Transforming, 2004). Homoscedasticity will be analyzed using Levene’s test. A 2-way repeated measures analysis of variance (ANOVA) will be used to determine the effects of interventions. The effects of the model are the group (GE; GC), the times (Pretest; Posttest), and their interaction over time (Time x Group). The effect size (ES) will be determined using Cohen’s d (<0.2 insignificant; ≥0.2 and ≤0.49 small; ≥0.5 and ≤0.79 moderate; ≥0.8 large) (Cohen, 2004). Additionally, in clinically relevant outcomes (risk of fall), the minimum clinically important difference (MCID) will be evaluated. All analyses will be performed with SPSS® v.26 (SPSS, Inc., Chicago, IL, USA), considering p < 0.05 and GraphPad Prism® v8.

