### Power calculation

3.3

The sample size was calculated as *a priori* using G*Power 3.1.9.7. Forty-six participants in total are required (23 in each group), considering α = 0.05, 1-β = 0.8, and effect size (ES) = 0.8 (Lower limb strength based on the results of a previous study) Considering the possibility of dropouts percentage, six participants were added (see Figure 1).

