### Randomization

3.5

The sample was selected from among those attending the SENAMA day center, reaching a size of 52 participants. The selection was randomized among those who met the inclusion and exclusion criteria. Participants were selected according to predefined inclusion and exclusion criteria. Inclusion criteria comprised adults aged 60 years or older of both sexes, attending SENAMA day centers in the Metropolitan Region of Santiago, Chile, with a Mini-Mental State Examination (MMSE) score greater than 14 and a Barthel Index score above 60, indicating moderate to good functional independence. Participants were required to walk independently (with or without assistive devices), report no medical contraindications for physical exercise, and provide written informed consent. Exclusion criteria included recent bone fractures or acute myocardial infarction, severe cardiovascular or respiratory conditions, uncontrolled hypertension or diabetes mellitus, cognitive or sensory impairments limiting instruction comprehension, concurrent participation in other exercise programs, or inability to attend at least 80% of intervention sessions. Participants were randomized by research staff using a computer-generated sequence and concealed allocation to one of two groups (Rubenstein, 2006): the exergame-based training plus multicomponent exercise group (EE + ME group), which will receive an exergame-based program combined with multicomponent exercise, or (Pijnappels et al., 2008) the multicomponent exercise group alone (ME group), which will receive multicomponent exercise. A computer-generated simple randomization sequence stratified by gender, age, and falls risk was used to balance the groups by sex, age, ranges, and falls risk index (RRI) in both groups. The randomization sequence was concealed using sealed, opaque, sequentially numbered envelopes to ensure allocation concealment (see Figure 1).

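### The repeated-measures ANOVA names no treatment test, and its one relevant term is less precise than baseline-adjusted ANCOVA unless pre-post correlation is high

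*Protocol article*

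**What the plan says.** Under Statistical analysis, the protocol article fixes the model for all outcomes: "A 2-way repeated measures analysis of variance (ANOVA) will be used to determine the effects of interventions". It then lists the terms: "The effects of the model are the group (GE; GC), the times (Pretest; Posttest), and their interaction over time". The significance level is p < 0.05. Neither the baseline value nor any other covariate is in the model, and the section does not say which of the three effects answers the trial's question.

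The Procedure section gives one assessment before the intervention and one after the 12-week programme, so each outcome contributes exactly two values per person. Under Randomization, "A computer-generated simple randomization sequence stratified by gender, age, and falls risk was used to balance the groups"; none of these factors is among the listed model terms.

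Under Power calculation, 23 per arm are required, "considering α = 0.05, 1-β = 0.8, and effect size (ES) = 0.8", and six participants are added for dropout, giving 52 (26 per arm).

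**The concern.** Two things look wrong.

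First, three effects are put forward to determine what the interventions do, and only one of them compares the arms after treatment. The abstract and the Discussion both expect each programme to improve outcomes. A significant Time effect is therefore likely even if exergames add nothing to multicomponent exercise. If no term is named in advance, that effect could be reported as support for the intervention. A null Group effect could likewise be read as equivalence, when that term is only weakly sensitive to a real difference.

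Second, in a trial of 52 people comparing two active exercise programmes, precision is scarce. The baseline value of every outcome is measured. Using it as one half of a change score gives a less precise estimate than using it as a covariate.

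**Working it through.** **Inputs.** From the article: 23 per arm before the dropout allowance, 26 per arm as planned, effect size 0.8, alpha 0.05, one pretest and one posttest. Assumed, because the article does not state them: a two-sided test, an effect size in units of the posttest SD σ, equal SDs at both times, and r over a range.

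**The plan's own figure.** A two-sample t test with effect size 0.8, alpha 0.05 and power 0.80 needs 26 per arm two-sided or 21 per arm one-sided. Neither gives the stated 23, at which two-sided power is 0.76. That is a separate matter. The calculation is described as resting on "Lower limb strength based on the results of a previous study" and does not refer to the repeated-measures model or to r, so it does not show what power the planned analysis has.

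**What each term estimates**, for a true 12-week difference δ under randomisation:

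- Time x Group: the difference in mean change. It estimates δ, with per-person variance 2(1−r)σ².
- Group: the difference between arms in the mean of pretest and posttest. The pretest difference is zero in expectation, so it estimates δ/2, with variance σ²(1+r)/2.
- Time: the average change over both arms. It contains no between-arm contrast.
- ANCOVA of posttest on arm and baseline: estimates δ, with variance (1−r²)σ².

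**Ratio.** (1−r²) / [2(1−r)] = (1+r)/2, which is below 1 for every r below 1.

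**Power.** Noncentral t with noncentrality (effect/σ) × √(n/2) / √v, where v is the variance factor above. Degrees of freedom are 2n−2, or 2n−3 for ANCOVA. At n = 23, √(23/2) = 3.391. For r = 0.5:

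- Time x Group: 0.8 × 3.391 / √1.00 = 2.71, power 0.76.
- ANCOVA: 0.8 × 3.391 / √0.75 = 3.13, power 0.86.
- Group: 0.4 × 3.391 / √0.75 = 1.57, power 0.34.

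For δ = 0.8σ and 23 per arm:

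| r | 2(1−r) | 1−r² | ANCOVA/change variance | Power, Time x Group | Power, ANCOVA |
|---|---|---|---|---|---|
| 0.3 | 1.40 | 0.91 | 0.65 | 0.61 | 0.79 |
| 0.5 | 1.00 | 0.75 | 0.75 | 0.76 | 0.86 |
| 0.7 | 0.60 | 0.51 | 0.85 | 0.93 | 0.96 |
| 0.8 | 0.40 | 0.36 | 0.90 | 0.99 | 0.99 |

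With 26 per arm the pairs are 0.67 and 0.84 (r = 0.3), 0.81 and 0.90 (r = 0.5), and 0.95 and 0.98 (r = 0.7). For 80% power the change-score test needs 36, 26 and 16 per arm at those correlations; ANCOVA needs 24, 20 and 14. For a smaller difference of 0.5σ (assumed) at 23 per arm and r = 0.5, power is 0.38 against 0.48.

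**Cost of further covariates.** The ANCOVA column has arm and baseline only. Simulation with 20,000 runs at 23 per arm, adding three covariates with no prognostic value, gives about 0.83 at r = 0.5, 0.94 at r = 0.7 and 0.99 at r = 0.8. Almost all of this loss comes from chance imbalance in the added covariates; the lost degrees of freedom alone cost under 0.003.

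**The case against.** The strongest reply is that nothing here is invalid. The model contains Time x Group, which is an unbiased test of the between-arm difference under randomisation. Every two-way ANOVA also has two main effects, and the stated objective is a between-arm comparison. This stands: a reader might infer that the planned analysis gives biased or invalid results, and the article does not support that. But the article fixes the model and its terms explicitly, so the choice is not a detail left to an unseen analysis plan.

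The size of the gain can also be disputed. It depends on an r that the article does not give. The Downton index is built partly from prior falls, medication and sensory deficits, which may change little in 12 weeks, so r could be high for that outcome and the gain close to nil. The article also does not say whether its effect size is in units of posttest SD or change SD. This stands, and it is why a range is shown.

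Two stronger readings should not be drawn.

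- A reader might infer that leaving out the stratification factors makes the standard errors wrong. The Randomization section calls the sequence simple as well as stratified and mentions no blocks, so a restriction that the standard errors fail to reflect is not established. Stratum effects that are constant over time cancel in Time x Group.
- The sentence "a two-step approach for transforming will be applied to the non-normal variables" might be taken to mean that pretest and posttest of one outcome could end up on different scales, or that the Downton score loses its points scale before its minimum clinically important difference is judged. The article does not say that the two time points are handled separately, nor that the Downton score will be transformed, and the clinical-importance evaluation is described as additional.

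**Conclusion.** The point holds as one of efficiency and specification, not validity. The article offers three effects without naming the treatment test. The Group term estimates half the difference (power 0.34 at r = 0.5 for 0.8 SD and 23 per arm), and the Time term is an uncontrolled before-after comparison. The one relevant term has 2/(1+r) times the variance of baseline-adjusted ANCOVA: 1.54 times at r = 0.3, 1.33 at 0.5, 1.18 at 0.7 and 1.11 at 0.8. In power, the gain from ANCOVA on baseline alone is 18 percentage points at r = 0.3, about 11 at r = 0.5, 3 at r = 0.7, and negligible from r = 0.8 upward. These figures assume equal SDs at the two times, a two-sided test and an effect of 0.8 posttest SD. The need to name one treatment contrast does not depend on r.

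**What to change.** For each continuous outcome, replace the two-way ANOVA with a linear regression (ANCOVA) of the 12-week value on arm and the baseline value of that outcome, adding sex, age and fall risk in the form used for randomisation. When the Downton index is itself the outcome, enter its baseline only once. State that the adjusted between-arm difference, reported with its 95% CI, is the only test of treatment effect, and that within-arm change is reported descriptively. If the ANOVA is kept, the minimum is one sentence naming Time x Group as the treatment test.

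The cost is wording. The baseline values are already in the assessment schedule, the model runs in the named software, and it combines with the planned multiple imputation. The downside is that each added covariate without prognostic value costs a little precision (power about 0.83 rather than 0.86 at r = 0.5 with three of them), and at r of 0.8 or more there is practically no gain over change scores. The text should be settled before any unblinded analysis.

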## Discussion

4

The primary objective of this study is to evaluate the effectiveness of a supervised exergame-based plus traditional multicomponent intervention compared to a traditional multicomponent training program in older adults at risk of falling. Based on the literature, it is hypothesized that both interventions will yield positive effects on primary and secondary outcomes. However, it is expected that the exergame-based program may result in equal or superior outcomes compared to the traditional intervention. This expectation is based on evidence suggesting that exergames can enhance exercise adherence and promote sustained engagement, which are often barriers in older adults (Valenzuela et al., 2018). Exergames have been described as an effective strategy to improve adherence to physical activity, particularly when integrated with social interaction and individualized support. Previous systematic reviews and meta-analyses have shown that exercise-based interventions benefit multiple domains of health in older adults, including functional capacity, balance, cardiorespiratory fitness, muscle strength, and quality of life, while also reducing fall risk (Fang et al., 2020; MacDermid et al., 2019; Ferreira et al., 2023; Ahn and Kang, 2023; A Two-Step Approach for Transforming, 2004; Cohen, 2004). These outcomes align with the anticipated benefits of both interventions in this study. However, while exergames show promise, there is limited evidence regarding their long-term impact on physical activity levels and fall prevention in older adults (Reis et al., 2019; Schoene et al., 2013). Additionally, exergames require specific equipment, and the cost of this technology remains a potential barrier for widespread implementation in day centers or community-based settings (Kari, 2014; Digitally, 2016).

While the potential benefits of incorporating exergames in elderly care settings are clear, challenges such as motivation to engage in physical activity, the perception of reduced social support when attending non-group-based interventions, and the financial cost of technological devices must be considered (Schürch et al., 2023). Despite these challenges, the personalized nature of the exergame-based program in this study, with direct supervision from trained professionals, is expected to mitigate some of these limitations by ensuring adherence to exercise guidelines and encouraging consistent engagement.

### Strengths, limitations, applications, and future research

4.1

A key strength of this study lies in its relevance and timeliness as a study protocol focused on fall prevention and functional improvement in older adults through exergame-based and multicomponent exercise interventions. The topic is highly pertinent given the growing need for innovative, technology-supported physical activity strategies addressing the challenges of ageing populations. Nevertheless, a potential limitation concerns the difficulty of achieving adequate exercise adherence among older adults, particularly when compared to established programs such as Vivifrail®. In terms of applications, this project underscores the importance of implementing such interventions worldwide, as aging and falls represent a significant and ongoing global public health concern. Future research should explore the development of exercise protocols incorporating other types of virtual reality environments, as well as the creation of accessible digital platforms for older adults who are unable to attend in-person sessions at community or care centers.

